## Abstract

**Background:**

Bronchopulmonary dysplasia (BPD) is still a common complication in very premature infants. At present, there is no effective treatment for BPD. Glucocorticoids are drugs commonly used to prevent or treat BPD before and after birth. In very premature infants with high risk factors for BPD, early use of dexamethasone can reduce the rate of death and/or BPD but may cause long-term adverse neurodevelopmental outcomes. Hydrocortisone (HC), as an alternative drug to dexamethasone, has been increasingly used to prevent BPD. However, no study has reported the efficacy and safety of HC to treat early BPD diagnosed at postnatal day (PND) 28.

**Methods:**

This study protocol is for a multicenter double-blind randomized controlled trial of low-dose HC in the treatment of early BPD. Early BPD infants will be randomly assigned to the HC treatment group or control group. Infants in the HC group will receive 0.5 mg/kg HC twice a day for 7 days and then 0.5 mg/kg HC once a day for 3 days. The control group will be given the same volume of placebo and no intervention on the basis of routine treatment. The primary outcome is survival without moderate or severe BPD at 36 weeks postmenstrual age. Secondary outcomes are the short- and long-term effects on growth, metabolism, neurodevelopment, and other possible complications.

**Discussion:**

This trial will determine the efficacy and safety of low-dose HC administration compared to placebo for the reduction of moderate or severe BPD at 36 weeks postmenstrual age in very preterm infants with early BPD.

**Trial registration:**

China Clinical Trial Registration Center ChiCTR1900021854. Registered on 13 March 2019.

## Background

Bronchopulmonary dysplasia (BPD) is a serious complication in very preterm infants, and the incidence has been no significant decrease in the past two decades [1]. When BPD is present in preterm infants, mortality and short- and long-term comorbidities are increased, and the need for health and education services is required more frequently than non-BPD infants later in life [2]. Since BPD was first described by Northway in 1967, the understanding of the pathophysiology evolved, and the definitions of BPD changed over time [3]. In 2001, the National Institute of Child Health and Human Development (NICHD) workshop defined BPD as the need for supplemental oxygen on the 28th day of life and categorized it as “mild, moderate, and severe” at 36th week postmenstrual age (PMA) (or 56 days of age for infants > 32 weeks GA), based on oxygen use and/or respiratory support [4]. Although this definition is widely used, its prognostic value is limited due to its inconsistent correlation with long-term respiratory outcomes and the inability to classify infants dying from severe respiratory failure prior to 36 weeks of PMA [5]. Thus, the Vermont-Oxford Network modified the BPD definition to need for oxygen supplementation at 36th week PMA [6, 7], perceiving a high accuracy in predicting long-term respiratory outcomes but being unable to guide the early treatment of BPD.

Inflammation plays a key role in the pathogenesis of BPD by providing the rationale for treating BPD with glucocorticoids, which have potent anti-inflammatory effects [8, 9]. A large number of studies have shown that glucocorticoids, especially dexamethasone, improve short-term pulmonary function in evolving BPD, but there is no evidence for beneficial long-term pulmonary outcomes. Since the reports by Shinwell et al. [10], concerns regarding adverse neurodevelopmental outcomes of premature infants exposed early to dexamethasone have increased [11, 12]. Supported by a systematic review, the actual conclusion of this debate is that the short-term benefits of postnatal dexamethasone do not outweigh the long-term adverse effects. Thus, dexamethasone is recommended only for infants who cannot be weaned from mechanical ventilation more than 7 days after birth [11–13].

As an alternative glucocorticoid, hydrocortisone (HC) has been considered to replace dexamethasone [14, 15]. In newborn rats, HC had no detrimental effect on neurodevelopment [16], and infants exposed to HC in neonatal life had a higher median motor optimality score at the age of 3 months compared to those with dexamethasone exposure [17]. Furthermore, some studies have indicated that exposure to low-dose HC (1–2 mg/kg/d) leads to increased survival without BPD [9, 18–21] and does not increase adverse long-term neurodevelopmental sequelae [22–25]. However, these studies only used HC as a prophylactic drug (started at ≤ 7 days or between 7 and 14 days after birth) [9, 18–26].

In current clinical practice, according to the NICHD criteria, 68–77% of very preterm infants are diagnosed with BPD at 28 days of life (early BPD), while approximately 60% of early BPD infants still need oxygen or respiratory support at a PMA of 36 weeks (moderate or severe BPD) [27–29]. Thus, it is essential to find an effective and safe drug to prevent early BPD from developing to moderate or severe BPD. However, based on the current recommendations, except those needing mechanical ventilation, very preterm infants will not be treated with glucocorticoids at this stage. Based on the use of early low-dose HC in infants with a high risk of BPD in previous studies [9, 18–25], an RCT study is reasonable to evaluate the efficacy and safety of low-dose HC in treating early BPD.

## Study design and methods

### Aim of the study

To investigate the efficacy and safety of a low dose of HC in the treatment of early BPD, diagnosed at postnatal day (PND) 28 in preterm infants.

### Study design

This multicenter double-blind randomized controlled trial will be performed at three centers in China. The enrollment period will be 1 year, and there will be a series of follow-up for every child until 2 years corrected age, which is the revised age from the 40th gestation week for a premature baby. The human research ethics committees at each participating center approved the trial, and an independent academic board will monitor the trial.

### Participants

Inclusion criteria:
Gestational age 26^+0^ to 30^+6^ weeks and birth weight < 1500 g; andDiagnosed early BPD at day 28, based on NICHD criteria [4] and never received any glucocorticoids after birth; andOne of the following conditions:
Oxygen reduction test showing SpO_2_ < 90% with FiO_2_ > 0.3 orNoninvasive ventilation support or nasal cannula with FiO_2_ > 0.21.

Exclusion criteria included any of the following conditions:
Invasive ventilation support needed on the 28th day of life.Congenital malformations affecting pulmonary function (e.g., congenital surfactant protein deficiencies, congenital diaphragmatic hernia) or increasing the risk of death or adverse neurodevelopmental outcome (e.g., congenital cerebral malformations, congenital hydrocephalus).Chromosomal defects (e.g., trisomy 13, 18, 21).Severe infection less than 7 days before randomization (late-onset sepsis/meningitis confirmed by positive blood culture; bacterial pneumonia, confirmed by positive tracheal culture; neonatal necrotizing enterocolitis).

### Sample size calculation

According to the data from the participating centers in the past 2 years and the data presented from the range of previous studies [27–29], the incidence of early BPD in infants with gestational age 26^+0^ to 30^+6^ weeks was 68–77%, and 40% developed moderate or severe BPD. The effect of HC therapy was assumed to reduce moderate or severe BPD (the primary endpoint) to 25% or less (number needed to treat, NNT = 5). Adopting a maximum significance level of *α* = 0.05 and a minimum test power of 80%, the number of subjects per group will be *N* = 81, which will be increased by 20% to compensate for potential dropouts during the follow-up, leading to 98 subjects per group (total 98 × 2 = 196 subjects).

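### 81 infants per group (98 randomised) give 53% to 61% power for the stated fall from 40% to 25%, not 80%; N = 81 and NNT = 5 both belong to a fall to 20%

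*Protocol article*

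**What the plan says.** The section *Sample size calculation* of the protocol article gives a complete set of inputs:

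- Control rate: "the incidence of early BPD in infants with gestational age 26^+0^ to 30^+6^ weeks was 68–77%, and 40% developed moderate or severe BPD".
- Effect: "The effect of HC therapy was assumed to reduce moderate or severe BPD (the primary endpoint) to 25% or less", followed in brackets by "number needed to treat, NNT = 5".
- Error rates: α = 0.05 and "a minimum test power of 80" per cent.
- Result: "the number of subjects per group will be *N* = 81".
- Dropout: "which will be increased by 20% to compensate for potential dropouts during the follow-up, leading to 98 subjects per group", or 196 in total.

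Neither the formula nor the sidedness of the test is given. The section *Statistical analysis* names the chi-square test for the primary outcome.

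**The concern.** The stated HC rate does not agree with the NNT beside it, and neither the NNT nor the 25% rate needs a formula to check: a 15-point difference is not an NNT of 5. The sample size appears to follow the NNT and not the rate. If so, the power claim does not hold for the effect the paragraph puts in words.

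This paragraph is the only justification printed for the size of a randomised trial in very preterm infants. If HC achieves exactly 25%, the trial would miss the effect far more often than the 20% that readers, ethics committees and the academic board would infer from it.

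**Working it through.** **Inputs.** Control rate p1 = 0.40, HC rate p2 = 0.25, α = 0.05, power 0.80, equal groups, all from *Sample size calculation*; chi-square test from *Statistical analysis*. Two-sided testing is assumed, and one-sided is tried as well.

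**Step 1: NNT.**
- 40% to 25%: 1/(0.40 − 0.25) = 6.7.
- 40% to 20%: 1/(0.40 − 0.20) = 5.

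**Step 2: where 81 comes from.** With p̄ the mean of the two rates, the pooled-variance formula for n per group is

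n = [1.960·√(2p̄(1−p̄)) + 0.842·√(p1(1−p1) + p2(1−p2))]² / (p1 − p2)²

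For 40% vs 20%, p̄ = 0.30:

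n = [1.960·√0.42 + 0.842·√0.40]² / 0.04 = (1.270 + 0.532)² / 0.04 = **81.2**

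The arcsine formula gives 80.3, which rounds up to 81. Power at 81 per group is 79.9% (80.2% by exact enumeration of the chi-square test). The plan's figure is therefore reproduced, but with 20% in the HC group.

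**Step 3: the stated 25%.** p̄ = 0.325:

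n = [1.960·√0.43875 + 0.842·√0.4275]² / 0.0225 = (1.298 + 0.550)² / 0.0225 = **151.9, so 152**

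| Variant, 40% vs 25% | n per group |
|---|---|
| Two-sided, pooled | 152 |
| Two-sided, unpooled | 150 |
| Two-sided, arcsine | 152 |
| Two-sided, continuity-corrected | 165 |
| One-sided, pooled | 120 |
| One-sided, unpooled | 118 |
| One-sided, continuity-corrected | 133 |

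None comes near 81.

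**Step 4: power for 40% vs 25%.** Power = Φ[(0.15·√n − 1.298) / 0.654]:

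- n = 81: (1.350 − 1.298)/0.654 = 0.079, power **53.2%** (exact chi-square 53.9%)
- n = 98: (1.485 − 1.298)/0.654 = 0.286, power **61.2%** (exact chi-square 61.6%)
- n = 78: power 51.6%

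One-sided, the figures are 65.5% at 81 and 72.7% at 98. With a 40% control rate, two-sided power reaches 80% only at an HC rate of about 20.0% (81 per group) or 21.6% (98 per group).

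**Step 5: other control rates.** The *Background* says about 60% of early BPD infants still need oxygen or respiratory support at 36 weeks. Two-sided, 60% vs 25% needs 31 per group, 60% vs 40% needs 97 and 60% vs 45% needs 173. A 45% vs 25% comparison also has NNT 5 and needs 89. It gets close to 81 only one-sided with continuity correction (79), and the article states no 45% rate.

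**Step 6: dropout.** 81 × 1.2 = 97.2, so 98. Losing 20% of 98 leaves 98 × 0.8 = 78.4. To retain 81 after 20% loss needs 81/0.8 = 101.25, so 102. With 98 per group the tolerable loss is 1 − 81/98 = 17%.

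**The case against.** The strongest replies concern the reading and the remedy.

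- **25% or less includes 20%.** It does, but 25% is the weakest effect inside that assumption and 80% is stated as a minimum power. A minimum has to hold at 25%, where it does not.
- **Two of the three figures agree.** NNT = 5 is also a stated assumption, and with a 40% control rate it fits N = 81. This stands: 25% is the outlier and may be a slip. The paragraph supports 80% power under one of its own assumptions and 53% under another.
- **The trial randomises 98, not 81.** The 20% is for loss during a follow-up that runs to 104 weeks corrected age, whereas the primary outcome is read at 36 weeks PMA. Infants enter at day 28, at about 30 to 35 weeks PMA, so little loss before that point is plausible. This stands as a reason to look at 61% as well as 53%. It does not bring the power to 80%.
- **The dropout arithmetic is correct as worded.** The text says N is increased by 20%, and it is. Multiplying instead of dividing costs 4 infants per group, which is minor.
- **The 40% may itself be wrong.** Taking 60% of the 68–77% with early BPD gives 41–46% of all very preterm infants, so 40% could be a whole-population rate, while only infants with early BPD are randomised. With 60% vs 40%, power is 72.5% at 81 and 80.4% at 98. This does not repair the paragraph, but it means that replacing 25% by 20% could leave another wrong figure in place.

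**Conclusion.** The concern holds. For the stated fall from 40% to 25%, 81 per group gives about 53% power and all 98 about 61%, against a claimed minimum of 80%; the corresponding risk of missing the effect is 47% and 39%. For 80% power, about 152 evaluable infants per group would be needed. NNT = 5 and N = 81 both match 40% to 20%.

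These figures assume a two-sided 5% chi-square test, equal groups and the 40% control rate of the sample size section. One-sided testing does not change the conclusion (120 per group needed; 73% power at best with 98). The dropout allowance is a small secondary point on which the conclusion does not depend.

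**What to change.** Correct *Sample size calculation* so that rate, NNT, N and power agree, and state the sidedness and formula used. First say whether 40% refers to infants with early BPD, and reconcile it with the roughly 60% in the *Background*. Then choose one:

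1. **Keep 25%.** Give NNT as 6.7 and state the power as 53% with 81 evaluable per group and 61% with 98.
2. **State 20%.** Give a 20-point difference, NNT = 5, 81 per group and 80% power. This is right only if 20% against a 40% control rate was the real assumption; it should not be fitted to the sample size afterwards.

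In either case, say that 98 per group tolerates 17% loss before falling below 81.

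The cost is one rewritten paragraph, a check of the control rate and, under the first route, a less favourable power figure. No change in enrolment is required. Should the sponsor want 80% power at 25%, that is 152 evaluable per group, or 152/0.8 = 190 randomised per group with 20% loss.

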### Trial medication and dosing

Trial medication will be prepared and distributed according to Good Clinical Practice (GCP) and Good Manufacturing Practice (GMP) guidelines. Using a double-blinded, placebo-controlled design, infants will be allocated to either HC or placebo treatment.

The long-term adverse neurodevelopmental outcomes observed with dexamethasone use are associated with the accumulative dosage [30]. The optimal (cumulative) dose of HC is currently unknown. In one previous study, Baud et al. [21] found that an early (< 7 days) low dose of HC increased the rate of survival without BPD at 36 weeks PMA without adverse neurodevelopmental outcomes at 2 years of age [22, 24]. Based on these findings, we adopted this dosage in the present study. Infants randomly assigned to the HC group will receive 0.5 mg/kg HC twice per day for 7 days, followed by one dose of 0.5 mg/kg per day for 3 days. This leads to a total duration of therapy of 10 days and a cumulative dose of 8.5 mg/kg HC. The control group will receive an equal volume of saline and will not receive any other intervention on the basis of routine treatment.

### Use of cointervention

All randomized patients will be subjected to cointerventions, such as respiratory support and comedication, according to the guidelines and protocols of the participating centers. The participants will not be given other treatments outside of the trial interventions and cointerventions.

### Informed consent

Professional researchers will carefully introduce the detailed procedures, probable benefits, and potential risks of the study to the guardian of the infants who meet the inclusion criteria. The infants’ guardians will indicate their willingness to participate voluntarily by signing an informed consent form.

### Randomization

Eligible patients will be randomized at day 28 after birth in each center after at least one guardian provides informed consent. A list of all eligible patients not included in the study will be provided from all centers throughout the time of enrollment. This trial will be protected from selection bias by using concealed, stratified, and blocked randomization. Randomization will be stratified according to gestational age stratum (26^+0^ to 28^+6^ weeks, and 29^+0^ to 30^+6^ weeks) in each study center. Multiple birth infants will be internally randomized. The randomization procedure will be generated by using Excel software by the GCP faculty at the participating hospitals, and it will be sealed in a sequentially numbered envelope to maintain the allocation concealment. According to the allocation sequence, drug packages will be hidden and labeled sequentially. Participants will receive packaged drug in the order of recruitment. The first dose of study medication will be administered within 1 h after randomization.

The complete random sequence will be kept by the primary researcher at the affiliated hospital of Southwest Medical University. Centers will individually have emergency envelopes that contain the treatment information for patients. Emergency envelopes can be unsealed only under special conditions.

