### Clinical data collection

At the time of randomization, baseline data will be collected from all included patients, including maternal and patient characteristics. Demographic data will include sex, birth weight, gestational age, 5-min Apgar score, surfactant therapy, prenatal corticosteroid use, premature rupture of the membrane before the onset of labor (> 18 h), singleton/multiple birth, and mode of delivery. Population characteristics will be used to compare outcomes between the two groups.

The following clinical data will be collected: continuous positive airway pressure (CPAP)-assisted time, invasive ventilator-assisted time, days of hospitalization, days on supplemental oxygen, IVH, spontaneous intestinal perforation, NEC, and ROP.

During HC treatment, respiratory support, blood sugar, blood pressure, and anthropometric data will be collected. Outcome variables and cointerventions will be recorded at 36 weeks PMA.

After discharge, one trained investigator in each center will follow up all patients at 40 weeks PMA and at 12, 26, 52, and 104 weeks corrected age. We will provide free neurodevelopmental impairment examinations to promote follow-up rates. For potential dropouts during the follow-up, we will expand the sample size by 20% and the missing data will be ignored in the analysis. The outcomes at each time point mentioned above will be collected by the investigators (Table 1).

**Table 1 Tab1:** SPIRIT figure: showing time points for enrollment, interventions, and assessment

	Study period						
	Enrollment	Allocation	Post-allocation				Close-out
Time point	At 4 weeks after birth	At 4 weeks after birth	At 36 weeks postmenstrual age	At 40 weeks postmenstrual age	At 12, 26 weeks corrected age	At 52 weeks corrected age	At 104 weeks corrected age
Enrollment:							
Eligibility screen	X						
Informed consent	X						
Demographic data	X						
Allocation		X					
Intervention:							
Hydrocortisone		X					
Placebo		X					
Assessments:							
Baseline variables assessments	X	X					
Primary outcome			X				
Secondary outcomes:							
Brain volume				X			
Others			X				
Long-term outcomes:							
Neurodevelopmental impairment, hearing loss, and blindness							X
Number of readmissions						X	
Weight, length, and head circumference				X	X	X	X
Behavioral problems, premature birth-related mortality							X

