### Statistical analysis

The analyses will be based on the intention-to-treat (ITT) principle in accordance with the Consolidated Standards of Reporting Trials (CONSORT). Statistical analyses will be performed with SAS version 9.2 (SAS Institute, Cary, North Carolina). Data will be presented as the mean ± standard deviation or median and interquartile range depending on their distribution. Categorical data, including the primary outcome, will be analyzed using the chi-square test between two groups. Continuous data will be analyzed using Student’s *t* test or the Mann-Whitney test as appropriate. The effect of HC on the dichotomous outcomes will be assessed by multivariable logistic regression analysis including possible confounders, including birth weight and gestational age. Statistical results will be reported as point estimates and 95% confidence intervals.

Mid-term data analysis will be conducted after inclusion of the first 98 patients. The principal investigator will decide whether any measure should be taken in light of the results. Case report forms (CRFs) will be entered by two independent researchers to ensure accuracy.

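### Respiratory status at entry, the baseline counterpart of the primary outcome, is neither a listed baseline variable nor a named covariate, and the primary outcome is tested by an unadjusted chi-square

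*Protocol article*

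**What the plan says.** All references are to the protocol article.

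- **Participants.** Beyond early BPD at day 28, an infant qualifies in one of several ways. One is an oxygen reduction test: "Oxygen reduction test showing SpO_2_ < 90% with FiO_2_ > 0.3". The others are noninvasive ventilation, or nasal cannula with FiO2 above 0.21. The upper end is cut off by an exclusion: "Invasive ventilation support needed on the 28th day of life".
- **Primary outcome.** Survival without moderate or severe BPD at 36 weeks postmenstrual age, defined by the absence of respiratory support and by saturation in room air.
- **Study design and Randomization.** The trial "will be performed at three centers in China". "Randomization will be stratified according to gestational age stratum", with two gestational-age strata in each center.
- **Clinical data collection.** "Demographic data will include sex, birth weight, gestational age, 5-min Apgar score, surfactant therapy, prenatal corticosteroid use", followed by membrane rupture, plurality and mode of delivery. Respiratory support appears later: "During HC treatment, respiratory support, blood sugar, blood pressure, and anthropometric data will be collected".
- **Statistical analysis.** "Categorical data, including the primary outcome, will be analyzed using the chi-square test between two groups". Dichotomous outcomes are also to be assessed by "multivariable logistic regression analysis including possible confounders, including birth weight and gestational age". The section does not say that this model takes precedence over the chi-square for the primary outcome.

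**The concern.** Support mode and FiO2 at day 28 are in effect the baseline value of the endpoint. Infants are born at 26+0 to 30+6 weeks and randomized at day 28, so they enter at 30+0 to 34+6 weeks postmenstrual age. The outcome is read at 36 weeks, about 1 to 6 weeks later. It is reasonable to expect entry status to predict the outcome well, although the documents give no figure for this.

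The listed baseline items all describe the pregnancy, the birth or the infant's initial care. None describes the lungs at day 28. If more of the sicker infants fall into one arm by chance, the listed baseline data would not show it and the chi-square would not correct for it. The covariate wording is open, so severity could still be added later. If that happened after an imbalance was seen, it would be a data-driven choice and open to challenge. Adjustment named in advance avoids this and also recovers power.

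**Working it through.** **1. The plan's own figures.** The sample size section gives a control risk of 40%, a risk on hydrocortisone of 25% or less, a number needed to treat of 5, 80% power, alpha 0.05, and 81 per group raised to 98.

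- 40% vs 25% (two-sided, pooled variance) needs 152 per group, so 81 is not reproduced. Power is 53% with 81 and 61% with 98.
- A number needed to treat of 5 implies 40% vs 20%, which needs 82 per group. This matches 81 closely.

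That discrepancy is a separate matter. It matters here only because the target difference may be read as 15 or 20 points, so both are used below.

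**2. Assumptions not in the documents.** A share q = 0.5 of infants is in a more severe entry group. Their risk of moderate or severe BPD is higher than that of the rest by a gap of 20, 30 or 40 points, with the average kept at 40% (30/50, 25/55 or 20/60).

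**3. Size of a chance imbalance.** The SD of the between-arm difference in the severe share is sqrt(2q(1−q)/n).

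- n = 98: sqrt(2 × 0.5 × 0.5/98) = 0.0714; 95% limit 1.96 × 0.0714 = 0.140.
- n = 81: sqrt(2 × 0.5 × 0.5/81) = 0.0786; 95% limit 0.154.
- An imbalance of 10 points or more has a probability of about 16% to 18% with 98 per arm (normal approximation and simulation).

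**4. Shift in the unadjusted risk difference** (imbalance × gap), in percentage points:

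| Gap | n = 98, 1 SD | n = 98, 95% limit | n = 81, 95% limit |
|---|---|---|---|
| 20 | 1.4 | 2.8 | 3.1 |
| 30 | 2.1 | 4.2 | 4.6 |
| 40 | 2.9 | 5.6 | 6.2 |

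With 98 per arm, 2.8 to 5.6 points is 19% to 37% of a 15-point effect (2.8/15, 5.6/15) or 14% to 28% of a 20-point effect (2.8/20, 5.6/20). With q = 0.3 the 95% shift is 2.6 to 5.1 points.

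**5. Type I error.** Simulation with 20,000 trials per scenario and 98 per arm puts the unadjusted test at about 5% overall. Among trials with an imbalance of 10 points or more, it is about 5% to 7% (gap 20), 7% to 8% (gap 30) and 9% to 10% (gap 40). A logistic model with the severity indicator stays near 5% in those same trials.

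**6. Power, unadjusted vs adjusted for the one severity indicator.** The ranges cover a constant risk ratio and a constant odds ratio.

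| Scenario | Unadjusted | Gap 20 | Gap 30 | Gap 40 |
|---|---|---|---|---|
| 98 per arm, 40% vs 25% | 61–62% | 63% | 65% | 67–68% |
| 81 per arm, 40% vs 20% | 80–81% | 81% | 82–83% | 84–85% |

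The gain is roughly 1 to 6 points, depending mainly on how strongly entry status predicts the outcome.

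**The case against.** Several objections carry weight.

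- **Randomization already protects the test.** The comparison is unbiased on average, and chance imbalance is part of what the test and the confidence interval allow for. This stands. A reader might infer that the primary result is biased or the test invalid; the documents and the calculation do not support that.
- **The lists are open.** The baseline and covariate sentences both use inclusive wording, and Table 1 schedules baseline assessments at enrollment and allocation. Support mode and FiO2 must in any case be read to establish eligibility. A reader might infer that entry severity will not be recorded at all; the article does not say so. What remains is that the article chooses its strata, baseline items, primary test and covariates explicitly, and the endpoint's own baseline value is in none of them.
- **Respiratory support is collected during treatment, with the first dose within an hour of randomization.** A first-day reading might come close to baseline. But it is not defined as a pre-dose value, and a post-randomization measure should not be used as a baseline covariate.
- **The range of severity can be overdrawn.** A reader might describe it as running from low-flow cannula to noninvasive ventilation above 0.3. The criteria do not say low-flow, they attach the 0.3 threshold to the oxygen reduction test, and they exclude invasive ventilation. The routes still differ clearly in respiratory state.
- **The sizes rest on assumed inputs.** This stands. Blocking by gestational age within center would also reduce the imbalance where severity follows gestational age. With severe shares of 70% and 30% in two equal strata, the SD is sqrt(2 × 0.21/98) = 6.5 points instead of 7.1, and the remaining risk gap would be smaller too.

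**Conclusion.** The point holds as a weakness in efficiency and robustness. It is not an error that invalidates the trial. The article leaves the entry value of the endpoint out of its listed baseline data and named covariates, and it tests the primary outcome without adjustment.

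Under the stated assumptions (half the infants more severe, a 20 to 40 point gap, 98 per arm), the cost is a possible uncorrected shift of 2.8 to 5.6 points at the 95% limit and about 1 to 6 points of power. The upper figures need a strong predictor; with a 20-point gap the power gain is only about 1 point. Describing the shift as more than a third of the target applies only to the 40-point gap and a 15-point effect.

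The absence of a severity stratum is not in itself the fault. There are already 3 × 2 = 6 strata for 196 infants, about 33 each, and a further two-level factor would halve that to about 16.

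**What to change.** 1. In Clinical data collection and Table 1, add respiratory support mode and FiO2 at randomization, recorded before the first dose, as baseline variables, and report them by arm.
2. In Statistical analysis, make the primary analysis of the primary outcome a prespecified logistic model of treatment adjusted for support mode, FiO2, gestational age and birth weight. Keep the chi-square test as supportive. Adding the covariates without this change of status would leave the primary test unadjusted.
3. Leave the randomization strata as they are.

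The cost is two case report form fields, already read to establish eligibility, and a short change to the analysis text. No visits, patients or procedures are added. One drawback is that the adjusted model gives a conditional odds ratio, which does not correspond directly to the risk difference used in planning. It should be reported with a standardised risk difference and its confidence interval.

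### Siblings are randomized as separate infants but analysed as independent ones; if they are split between arms, the planned intervals are too wide and precision is wasted

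*Protocol article*

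**What the plan says.** **Allocation.** The Randomization section says of siblings only that "Multiple birth infants will be internally randomized". It does not say whether siblings are forced into different arms or each allocated separately. The surrounding rules do not mention families: "Randomization will be stratified according to gestational age stratum" within each center, and "Participants will receive packaged drug in the order of recruitment".

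**Analysis.** The Statistical analysis section states "Categorical data, including the primary outcome, will be analyzed using the chi-square test between two groups". Continuous outcomes get a t test or a Mann-Whitney test. Dichotomous outcomes also get "multivariable logistic regression analysis including possible confounders, including birth weight and gestational age". It adds that "Statistical results will be reported as point estimates and 95% confidence intervals". No pairing, family term, random effect or clustered variance is named.

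**Data.** Multiplicity appears in the Clinical data collection section as a baseline item ("singleton/multiple birth, and mode of delivery"). The Sample size calculation section makes no allowance for siblings.

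**The concern.** Siblings share a mother, a center and a gestational age, so their outcomes can be expected to correlate. The protocol expects to enrol them, since it writes a rule for them. The chi-square, t and Mann-Whitney tests and ordinary logistic regression all take each infant as an independent observation. The standard error then depends on how siblings are allocated, which the text leaves open, and the analysis does not adapt to the answer.

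Precision is what is at stake. A trial of 196 infants that aims to judge both efficacy and safety should not report wider intervals than its data justify, because benefits and harms both become harder to see.

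**Working it through.** **The plan's own figure.** The documents give no figure that reflects siblings. The 81 per group before dropout is an ordinary independent-infant calculation: a two-sided comparison of 40% with 20% (the stated NNT of 5) at 80% power gives 82 per group, with no sibling term. That 81 does not fit the stated 25% is a separate matter and does not affect this point.

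**Inputs from the documents.** 98 infants per group; 40% rate of moderate or severe BPD; nominal alpha 5%, taken as two-sided.

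**Inputs assumed.** m, the share of enrolled infants whose sibling is also enrolled, and rho, the within-pair correlation. The documents give neither, so a range is shown.

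**Formula.** Let N be the number per arm and s² the outcome variance.
- The tests assume Var(difference) = 2s²/N.
- Of 2N infants, 2Nm are in pairs, which makes Nm pairs.
- If each pair is split between arms, every pair adds a covariance of rho × s² between the two arm totals. The variance of the difference falls by 2 × Nm × rho × s² / N² = (2s²/N) × m × rho.
- The ratio of true to assumed variance is therefore 1 - m × rho.
- The standard error is overstated by 1/√ratio - 1.
- The real alpha is 2 × (1 - Φ(1.96/√ratio)).
- The share of the achievable effective sample not used is 1 - ratio. The data are worth N/ratio independent infants per arm, and the plain test uses N.

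**Results, siblings split between arms.**

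| m | rho | Ratio | SE overstated | Real alpha | Effective sample unused |
|---|---|---|---|---|---|
| 0.1 | 0.2 | 0.98 | 1% | 4.8% | 2% |
| 0.2 | 0.4 | 0.92 | 4% | 4.1% | 8% |
| 0.3 | 0.6 | 0.82 | 10% | 3.0% | 18% |

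**Check by simulation.** With 196 infants, a 40% rate in both arms, split pairs and 40,000 trials per setting, the chi-square test rejected in 4.4% of trials at m = 0.2, rho = 0.3 and in 3.5% at m = 0.3, rho = 0.5. The formula gives 4.3% (ratio 0.94) and 3.4% (ratio 0.85).

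**Power that could be recovered.** A further simulation used 98 per arm, 40% against 25% and split pairs (20,000 trials). At m = 0.3, rho = 0.5, power was 62.7% with chi-square and 68.8% with a clustered analysis. At m = 0.2, rho = 0.3, it was 61.8% and 64.3%. A small part of the gain arises because the clustered test ran slightly above 5% (5.1% and 5.2%).

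**Siblings allocated independently.** In the same 196-infant simulation, chi-square type I error was 5.0% to 5.2% for m from 0.2 to 0.4 and rho from 0.3 to 0.7. The plain tests then have about the right width. This simulation tossed a coin for each sibling. With the planned blocks, siblings taking consecutive packs in one stratum would land in different arms somewhat more often than by chance, which moves the answer a little toward the split case. Block size is not given, so this is not quantified.

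**The case against.** **The independent reading has support.** Packs are numbered and handed out in order of recruitment, and the Randomization section describes no separate mechanism for forcing siblings apart. A second twin may simply take the next pack. This stands, and it makes the finding conditional. A reader might infer that all the trial's intervals and P values are certainly wrong, but the documents do not support that while the rule is undefined.

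**The error is conservative.** This also stands. With split pairs and a true 40% against 20% effect, simulated coverage of the nominal 95% interval was 95.2% to 96.5%, so a positive result remains valid. Nor does power fall below the design. Without siblings it is about 61% for 40% against 25% at 98 per arm, and the plain test with split pairs does no worse. What is lost is an available gain. A reader used to clustered designs might infer inflated false positives. That would require siblings to be kept in the same arm, which randomizing them internally does not suggest.

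**The size is assumed and may be small.** For a pair to count, both siblings must qualify at day 28 under the same criteria, including early BPD, no earlier postnatal glucocorticoids and no invasive ventilation, which limits m. Adjustment for gestational age and birth weight would absorb some of the correlation in the logistic model, so the table fits the unadjusted tests best. A reader might also expect a larger effect on growth or two-year scores, but the documents give no correlation for any outcome.

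**It could be left to the SAP.** Clustering often is. Here, however, the protocol itself commits the primary outcome to a chi-square test, so this is a stated method that fits the design poorly. Whether the case report form already links siblings cannot be told, because it is not shown.

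**Conclusion.** The point holds in conditional form. The protocol randomizes siblings as separate, correlated infants and fixes analyses that ignore the correlation. If siblings are split between arms, the plain standard error is too large by about 1% to 10% over the assumed values of m and rho, and up to about 18% of the achievable effective sample goes unused. If they are allocated individually, the plain width is about right and a clustered analysis does no harm. In neither case are false positives materially increased. This is a worthwhile improvement in precision and clarity and does not threaten the trial's validity. Its size rests wholly on m and rho, which the documents do not give, and its direction on a sibling rule that they do not define.

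**What to change.** - **Randomization section:** state whether siblings are forced into opposite arms or allocated individually, and how this works with the numbered packs.
- **Data:** make sure siblings can be linked, for example by a maternal identifier, if this is not already so.
- **Statistical analysis section:** cluster the primary and secondary analyses on mother. For dichotomous outcomes use GEE logistic regression or modified Poisson regression with robust variance. For continuous outcomes use a linear mixed model with a maternal random intercept. Keep the chi-square, t and Mann-Whitney tests as sensitivity analyses.

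The cost is some wording, at most one data field, and a slightly more complex model. No extra infants or visits are needed.
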